## Discussion

### Concerns about the 0/1-h algorithm

Cardiac troponin is the preferred biomarker of myocardial injury owing to its high specificity and sensitivity. In patients with suspected NSTE-ACS, serial sampling should be performed at presentation and after 3–6 h to demonstrate the existence of a rise and/or fall in troponin (or even earlier when high-sensitivity assays are used), as recommended since the third UDMI in 2012. The 0/1-h algorithm is recommended by the ESC guideline, based on its high safety and efficacy observed in multiple observational studies [14]. However, the clinical implementation of the 0/1-h algorithm in Europe and recently Northern America has not been without controversy due to the fact that the majority of the findings related to the 0/1-h algorithm were derived from highly controlled settings of observational, diagnostic studies [30, 31]. Similarly, the 0/1-h algorithm was derived in Central European patients. Shiozaki el al. reported Japan-Taiwan data [18, 26, 32]; however, particularly patients from Asian and African countries are largely underrepresented in the existing validation cohorts. As a result, the 0/1-h algorithm has not been introduced at some institutions in regular clinical practice.

### Characteristic of Asia

Compared with western countries, some countries in Asia showed much lower rates of coronary angiography and revascularization for patient with ACS, and also some of the highest post-discharge mortality rates [12, 22, 33–36]. This discrepancy highlights that quality of care is not only a matter of availability of resources but also depends on knowledge of guidelines and application of its recommendations, organization of care, including effective referral systems from secondary centers to tertiary centers with full coronary revascularization facilities, and issues related to social security coverage and/or need for reimbursement for procedures. The 0-h/1-h algorithm could aid the rapid transfer of high-risk patients to specialist cardiac facilities. These challenges can be best met by establishing cardiac networks and individual hospital models/clinical pathways taking into account local risk factors (including socioeconomic status), affordability and availability of pharmacotherapies/invasive facilities, and the nature of local healthcare systems.

### Study purpose

There are three complete randomized controlled trials that have been performed in this area. Two are from UK [24, 37], and the other is from Australia [10]. To expand the application of the 0/1-h algorithm in Asian countries, we intended to conduct a prospective, stepped wedge, cluster-randomized controlled approach, which will help evaluate the overall safety and efficacy of this novel approach. Asian countries are highly relevant as they represent a very large population with heterogenous medical settings. In general, when assessing novel diagnostic approaches with the potential to improve efficacy, clinicians always require evidence that safety of such a decision rule is non-inferior to standard of care. We also intend to compare the ED dwelling time as well as medical costs among Japan, Thailand, and Taiwan as a secondary endpoint. We hypothesize that the implementation of the 0/1-h algorithm has the potential to achieve an improved cost performance by the shortened ED dwelling time as well as the avoidance of unnecessary admissions or costly downstream cardiac examinations.

### Limitations

Our study is associated with several limitations. First, while the study is powered to document non-inferiority in safety of the 0/1-h algorithm compared with standard care, the targeted sample size does not allow to test for superiority in efficacy. Nevertheless, given the real-world design of this study with broad inclusion criteria, observations made within this study will provide important insights into the clinical utility of the 0/1-h algorithm in all-comers. Second, as the primary outcome, we assess the incidence of MACE within 30 days after index presentation in outpatients, which is the most relevant and best accepted measure to quantify safety of any triage algorithm in suspected ACS. However, we cannot comment on outcomes that occur beyond 30 days. Third, only Japan has a national registry named DPC to evaluate a whole medical cost related with the medical service in a following period. Other countries do not have. Therefore, in both Taiwan and Thailand, we will evaluate it in each hospital, individually. In the remaining centers, no data on cost-efficacy will be collected, which could cause some selection bias. Fourth, we cannot comment on the utility of the 0/1-h algorithm in patients with terminal kidney failure on chronic dialysis, because these patients were excluded from the initial studies deriving and validating this algorithm. Thus, patients on chronic dialysis will be excluded also in this study. Fifth, some selection bias may occur due to the need for consent in the intervention arm. Sixth, Juntendo University Nerima Hospital Juntendo University Urayasu hospital, and Tapei city hospital had a history to implement the 0/1-h algorithm. But during the usual care period, second measurement of troponin at 1-h interval will be prohibited.

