**Methods:**

The DROP-Asian ACS is a prospective, stepped wedge, cluster-randomized trial enrolling 4260 participants presenting with chest pain to the ED of 12 acute care hospitals in five Asian countries (UMIN; 000042461). Consecutive patients presenting with suspected acute coronary syndrome between July 2021 and Apr 2024 were included. Initially, all clusters will apply “usual care” according to local standard operating procedures including hs-cTnT but not the 0/1-h algorithm. The primary outcome is the incidence of major adverse cardiac events (MACE), the composite of all-cause death, myocardial infarction, unstable angina, or unplanned revascularization within 30 days. The difference in MACE (with one-sided 95% CI) was estimated to evaluate non-inferiority. The non-inferiority margin was prespecified at 1.5%. Secondary efficacy outcomes include costs for healthcare resources and duration of stay in ED.

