#### Primary outcome measure

The primary aim of the present study is to determine the relative safety of the 0/1-h algorithm compared with the current standard of care for patients presenting with suspected NSTE-ACS to the ED. Primary outcome measure is the incidence of major adverse cardiac events (MACE), defined as the composite of cardiovascular death, new acute myocardial infarction (AMI) (type 1 or 2), unstable angina, or unexpected revascularization within 30 days (defined as any unplanned hospitalization with cardiac revascularization performed within the first 12 h after hospital admission in the context of ACS). Of note, AMI diagnosed within 12 h of index presentation among participants continuously in-hospital will be considered as the index presenting AMI and not included as an endpoint event. An AMI documented to have commenced outside this time (recurrent/new AMI type 1 or 2) in hospitalized patients or within 12 h of index presentation among participants already discharged from the hospital (missed AMI type 1 or 2) will be considered an endpoint event.

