#### Secondary outcome measures

The following predefined secondary outcomes are considered:The proportion of patients managed as outpatients in order to quantify the efficacy of the investigated approaches in both arms.The time from ED presentation to discharge in outpatients. The ED dwell time is derived from a common electronic patient record system used across all participating sites and is calculated as the time of the medical examination between the start time (sign-in time: defined as first medical contact with a MD or the triage nurse) and the end time (sign-off time: defined as the time when the attending physician has finished all medical procedures in the ED, including charting, with the patient to ready to leave the examination room either to be discharged or transferred to a different unit/ward within the hospital).All-cause mortality (cardiovascular death and non-cardiovascular death) and new myocardial infarction (type 1 or 2) within 30 days after the index presentation.Incidence of any cardiac revascularization within 30 days after the index presentation.Incidence of ED representation or hospitalization for unstable angina within 30 days after the index presentation.Costs for healthcare resource use within 30 days following the index ED presentation are calculated based on each country’s guidelines and cost tables for hospitals. Different costs are used for academic and general hospitals. For each patient, the costs are calculated based on the observed number and type of healthcare resources used.Incidence of cardiac examinations (e.g., stress testing or coronary angiography) within 30 days after the index presentation. Adherence to the intervention condition (the 0/1-h algorithm) was evaluated.

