### Sample size, level of significance, and power

A survey of ED physicians found the tolerable rate of missed major adverse cardiac events to be less than 1% [19]; however, an analysis by Kline et al. showed that a 2% rate of missed diagnoses of ACS might be considered acceptable considering the risk of harm from further testing [20], and more than 2% of ACS patients are inappropriately discarded annually according to a Medicare database [21]. Regional differences in the management of NSTE-ACS persist in Asian countries even after extensive adjustment for baseline characteristics and treatment [12]. Indeed, in previous studies, the MACE rates tend to be higher than in Central European or North American countries and vary from 1 to 4% [10, 18, 22, 23]. We estimated that, in the standard care arm, patients managed as outpatients by usual care would experience an event rate of 3%, for the primary outcome of MACE including all-cause death, subsequent myocardial infarction, unstable angina, or unexpected revascularization in 30 days. The non-inferiority margin of 1.5% is based on clinical judgment and the available literature, thus, accepting an upper limit of the 95% confidence interval. No assumption was made about the level of intra-cluster correlation coefficient (ICC) [24]. Based on these numbers, a one-sided significance level of 5% and a power of 80%, the required total sample size for a stepped wedge design with 11 clusters was determined to be 4260.

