### Statistical analyses

Continuous variables will be presented as the mean (standard deviation) or median (interquartile range [IQR]), and categorical variables will be presented as numbers and percentages. The 30-day incidence of MACEs will be analyzed using generalized linear mixed models after adjusting for background information and seasonal effects. The clustering effect by hospital will be considered in this analysis as a random effect. The binomial distribution and identity link will be used to directly estimate the absolute differences in MACE incidence between 0/1-h algorithm care and usual care patients. The main model will include conditions (control or intervention) and steps (time periods) as categorical variables and hospitals as clusters. Differences in MACEs with a 1-sided 95% CI will be estimated in order to evaluate non-inferiority. The non-inferiority margin is preset at 1.5%. The sensitivity and negative predictive values (NPVs) for MACEs in the rule-out group and the specificity and positive predictive values (PPVs) for MACEs in the rule-in group will be calculated. Multiple imputations will be used to handle missing data. The statistical analyses will be performed using the SAS software program, version 9.4 (SAS Institute, Cary, NC, USA), and R version 4.0.3 (R Foundation for Statistical Computing, Vienna, Austria).

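### The primary analysis population is stated inconsistently: all patients presenting to the ED in some sections, outpatients only in others, and outpatient status is something the algorithm is meant to change

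*Protocol article*

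**What the plan says.** Two sets of statements in the protocol article point to different populations.

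**Towards all presenting patients**
- Primary outcome measure: the aim is the relative safety of the algorithm "compared with the current standard of care for patients presenting with suspected NSTE-ACS to the ED". Among the endpoint events is "An AMI documented to have commenced outside this time (recurrent/new AMI type 1 or 2) in hospitalized patients", listed separately from infarction missed in patients already discharged.
- Statistical analyses: the model is to "directly estimate the absolute differences in MACE incidence between 0/1-h algorithm care and usual care patients", with no restriction by disposition.
- Abstract, Methods: the trial is described as "enrolling 4260 participants presenting with chest pain to the ED of 12 acute care hospitals".

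**Towards outpatients only**
- Limitations: "as the primary outcome, we assess the incidence of MACE within 30 days after index presentation in outpatients".
- Sample size, level of significance, and power: the assumption is that "patients managed as outpatients by usual care would experience an event rate of 3" per cent.

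On how outpatient status arises, Secondary outcome measures lists first "The proportion of patients managed as outpatients in order to quantify the efficacy of the investigated approaches in both arms". The intervention section lets rule-out patients be considered for discharge, and Study purpose hypothesizes fewer unnecessary admissions.

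**The concern.** The population decides what the single non-inferiority test estimates. With the text as it stands, either analysis could later be called prespecified.

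The two choices are not equally sound. Disposition follows the troponin result, and the algorithm is intended to alter it. Patients discharged under usual care and patients discharged under the algorithm are therefore different selections from the same ED population, and randomizing the order of clusters does not make them comparable. A difference in outpatient MACE could then reflect who was sent home and not what happened to any given patient.

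There is also a planning mismatch. The 3% rate is labelled for outpatients, while 4260 is given as the number enrolled. If outpatients are analysed, fewer than 4260 contribute. If all patients are analysed, the 3% has not been justified for them.

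**Working it through.** **1. The plan's own figure.** Inputs from the sample size section: control rate 3%, margin 1.5 points, one-sided 5%, power 80%, total 4260, 11 clusters, no ICC assumed.

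A simple 1:1 non-inferiority formula gives, per arm, (1.645 + 0.842)² × 2 × 0.03 × 0.97 / 0.015² ≈ 1600, or 3200 in total. A stepped-wedge variance with equal cluster-period sizes, categorical steps and ICC 0 gives about 5277 without an excluded transition period and 6397 with one. So 4260 is not reproduced. The cluster-period sizes and the ICC behind it are not reported, so this is not evidence that 4260 is wrong. Below, 4260 for 80% power is taken as given.

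**2. Power if only outpatients are analysed.** Let f be the outpatient share, which is assumed because the article gives none. If information scales with the number analysed,

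power = Φ[(1.645 + 0.842) × √f − 1.645].

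| f | Analysed (4260 × f) | Power | Enrolment for 4260 outpatients (4260 / f) |
|---|---|---|---|
| 1.0 | 4260 | 80% | 4260 |
| 0.8 | 3408 | 72% | 5325 |
| 0.6 | 2556 | 61% | 7100 |

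The scaling is exact only without a cluster effect.

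**3. Power if all patients are analysed.** The rate for all patients may differ from 3% in either direction. The sample size section cites previous MACE rates of 1 to 4%. With equal true rates p in both conditions and 4260 analysed, power = Φ[2.486 × √(0.0291 / p(1−p)) − 1.645].
- p = 2%: √(0.0291/0.0196) = 1.218, so Φ(1.385) = 92%.
- p = 4%: √(0.0291/0.0384) = 0.871, so Φ(0.520) = 70%.

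**4. Selection with no effect on any patient.** All inputs here are assumed.

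*Illustration A.* Low, middle and high risk strata make up 60%, 25% and 15% of patients, with MACE of 0.5%, 4% and 11% whatever the care. The all-patient rate is 0.60 × 0.5 + 0.25 × 4 + 0.15 × 11 = 2.95% in both conditions, so the true difference is 0.

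| Discharged (low/mid/high) | Share discharged | MACE in outpatients | Difference from usual care |
|---|---|---|---|
| Usual care 70/50/15% | 56.75% | 0.9575 / 56.75 = 1.69% | – |
| Algorithm 90/50/15% | 68.75% | 1.0175 / 68.75 = 1.48% | −0.21 |
| Algorithm 90/30/5% | 62.25% | 0.6525 / 62.25 = 1.05% | −0.64 |
| Algorithm 90/70/30% | 76.00% | 1.4650 / 76.00 = 1.93% | +0.24 |

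*Illustration B.* Usual care discharges 60% of patients, with 3% MACE. The algorithm discharges a further 15%, whose MACE is 4% or 6%.
- 4%: (0.60 × 0.03 + 0.15 × 0.04) / 0.75 = 3.2%, a shift of +0.2 points.
- 6%: (0.60 × 0.03 + 0.15 × 0.06) / 0.75 = 3.6%, a shift of +0.6 points.

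Across both, the spurious difference runs from about −0.6 to +0.6 points. Against the margin that is 0.64/1.5 = 43% in the direction of false safety and 0.6/1.5 = 40% in the direction of false harm.

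**The case against.** The strongest reply is that the sections that define the outcome and the model carry no outpatient restriction. The outpatient wording sits in a Discussion sentence whose real subject is the 30-day horizon, straight after a sentence claiming insight into all-comers. On that view it is loose phrasing. This stands in part: an outpatients-only primary analysis is not specified in the methods, and a reader who infers that it is the plan goes beyond the text. Equally, no section says in terms that all enrolled patients are analysed; that reading rests on the counting of events in hospitalized patients and on the absence of a restriction elsewhere. But the wording is not a lone slip, because the sample size section also ties its rate to outpatients.

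A reader might also infer that 3% is too low because admitted patients must have more events. The article does not support this. Infarction diagnosed within 12 hours in patients continuously in hospital is excluded as an endpoint, which removes a likely source of inpatient events, and the earlier studies with rates of 1 to 4% are not described as outpatient cohorts. The direction of any error in the planning rate is unknown.

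Nor can the bias be assumed to run towards harm. If the algorithm mainly sends home more low-risk patients, which fits the hypothesized fall in unnecessary admissions, the outpatient contrast looks spuriously safe.

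Finally, analysing everyone does not give full protection. One cluster was added without randomization, and the article admits possible selection from consent in the intervention arm. That is true, but it is no reason to add conditioning on disposition.

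**Conclusion.** The inconsistency is real and unreconciled, and it concerns the population for the trial's only non-inferiority conclusion, so it must be resolved before analysis. What is established is the conflict in wording, the mismatch between the labelled population of the 3% rate and the enrolled 4260, and the fact that outpatient status is a post-allocation result.

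The sizes are conditional. The range of −0.6 to +0.6 points depends on assumed strata and discharge proportions and is not an estimate of bias in this trial. Power of 72% or 61% depends on assumed outpatient shares of 80% or 60%, on accepting 80% at 4260, and on information scaling with numbers analysed. A reader who recalculates the stepped-wedge power may be tempted to start from a figure below 80%. That would be a separate objection, resting on an assumed equal-cell layout that does not match the lengthened later steps or the low-enrolling cluster, and nothing here depends on it.

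**What to change.** 1. In the abstract, Primary outcome measure, Statistical analyses and Limitations, state that the primary analysis includes every eligible enrolled patient in a control or intervention period, whatever the disposition, analysed by the condition scheduled for that cluster and step. Transition-period patients stay excluded, as already planned.
2. Make 30-day MACE in discharged patients a secondary, descriptive outcome, reported beside the proportion managed as outpatients and without a non-inferiority claim.
3. In the sample size section, restate or justify the 3% rate for all enrolled patients, without presuming that it is too high or too low, and give the resulting power at 4260.

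The cost is wording in the protocol and any analysis plan, plus a planning rate or power figure that may turn out less favourable. No new data are needed. The article reports recruitment in progress with 2124 patients included, so the change can be made before the outcome comparison.

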## Conclusion

Asian countries represent the largest population in the world, but the region comprises many island nations, with no unified trends. As a result, there are regional differences in the degree of congestion in the ED. However, the degree of congestion is associated with a worsening of the patient prognosis, especially regarding patients with chest pain disease. The introduction of the 0/1-h algorithm is therefore expected to maintain high safety while reducing medical costs by shortening the medical treatment time, utilizing efficient patient stratification based on quantitative evaluations, and reducing the performance of excessively invasive medical treatments and unnecessary hospitalization. The national medical systems of these countries differ markedly, as do approaches to financing medical care.

### Trial status

The study is currently recruiting patients. As of Sep 30th, 2022, 2124 patients had been included. The first patient was included on July 1st, 2020, and inclusion is expected to be completed on October 14th, 2023.

## Data Availability

The final dataset will not be accessible for the research group of the DROP-Asian ACS study (the authors of this protocol). The datasets generated and/or analyzed during the current study are not publicly available, owing to protection of personal data.
